## Methods/design

### Study design

To assess the relationship between intraoperative arterial partial pressure of oxygen (PaO_2_) and the incidence of POCD and delirium we have designed a single-center, randomized, double-blind superiority trial of 100 participants with an allocation of 1:1. Subjects undergoing CABG surgery with CPB will be prospectively randomized to one of two different levels of fraction of inspired oxygen (FiO_2_) intraoperatively. The primary outcome of postoperative cognitive decline will be assessed via cognitive testing at baseline, daily from postoperative day 1 until hospital discharge, and then by phone at 1, 3, and 6 months postoperatively (Fig. 1 for trial schematic). Table 1 details the structured study summary according to the World Health Organization Trial Registration Data Set. The trial protocol was written in accordance with the Standard Protocol Items: Recommendations for Interventional Trials (SPIRIT) checklist [14] (Additional file 1).

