**Fig. 1 Fig1:**
[figure not shown]
Study schema

**Table 1 Tab1:** WHO Trial Registration Data Set - Structured Summary

Data category	Information
Primary registry, trial identifying number	Clinicaltrials.gov Identifier - NCT02591589
Date of registration in primary registry	February 13, 2015
Secondary identifying numbers	
Sources of monetary support	Foundation for Anesthesia Education and Research Mentored Training Research Grant
Contact for public queries	SS, Department of Anesthesia, Beth Israel Deaconess Medical Center, Boston MA, USA
Contact for scientific queries	SS, Department of Anesthesia, Beth Israel Deaconess Medical Center, Boston MA, USA
Public title	Intraoperative Oxygen Concentration and Neurocognition After Cardiac Surgery
Scientific title	The relationship between administered oxygen levels and arterial partial oxygen pressure to neurocognition in cardiac surgical patients
Country of recruitment	USA
Health problem under investigation	Neurocognition after cardiac surgery
Key inclusion and exclusion criteria	Age ≥ 65 years, elective or urgent coronary artery bypass surgery (CABG) on cardiopulmonary bypass (CPB)
Study type	Interventional Allocation: randomized Interventional model: Masking: blinding of participant and outcomes assessor
Date of first enrollment	September 2015
Target sample size	100
Recruitment status	Recruiting as of January 2017
Primary outcome	Change in Telephonic Montreal Cognitive Assessment from baseline up to 6 months
Key secondary outcomes	Delirium incidence, time to extubation, Acute kidney injury incidence

The SPIRIT figure (Fig. 2) demonstrates the schedule of enrollment, interventions, and instruments of assessment used in the trial.

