## Study outcomes and their measurement

### Primary endpoint

To assess the occurrence of POCD we will use the t-MoCA. Scores on the t-MoCA will be measured preoperatively and postoperatively, using a daily in-hospital assessment until discharge or 30 days, whichever is sooner. In order to reduce fatigue completing assessments, if t-MoCA scores have plateaued for three consecutive days and CAM assessments are negative, assessments will occur every third day in-hospital through a skip pattern algorithm.

The t-MOCA is an adaptation of the widely used MoCA assessment [16], with items requiring writing and picture recognition removed. T-MoCA results in a 22-point scale and has been validated as a marker for cognitive function [16, 17]. Additionally, there will be telephone follow-up and t-MOCA assessment at 1, 3, and 6 months postoperatively, which does not require that participants be assessed in person. The telephonic version of the MoCA was chosen as the cognitive test to be performed both in-person and in telephonic follow-up so as to have equivalent scoring between assessments at all follow-up time points throughout the study. In previous studies, testing to 6 months has been shown to accurately reflect longitudinal follow-up of cognitive trajectories after CABG [18, 19] and thus this was the time endpoint for the follow-up in our study. Blinded, specially trained study staff will administer the assessments and assist in data collection.

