## Statistical analysis

### Sample size calculation

Using previous data [3], and assuming a cross walk between t-MoCA and Mini-Mental State Examination (MMSE) [22], a two-sided α = 0.05 and 80% power, we will need 74 subjects in total to detect a mean difference in t-MoCA scores of 2 (standard deviation of 3) between the hyperoxia and normoxia group at postoperative day 2. This cognitive decrement was previously reported as clinically significant and postoperative day 2 was reported as the in-hospital postoperative nadir time point [19]. A total of 100 randomized subjects who have undergone the entire intraoperative intervention will be enrolled to allow for potential attrition from loss to follow-up or withdrawal.

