### Data analysis

Descriptive statistics of the data will be performed. Continuous data will be represented using mean (± standard deviation) or median (interquartile range) for variables not normally distributed and compared using parametric or non-parametric *t* tests as appropriate. Categorical data will be presented using proportions and compared using a chi-square (or Fisher’s exact) test. Two-sided *p* values less than 0.05 will be considered statistically significant. All analyses will be conducted using the intention-to-treat principle. No interim analyses are planned and there are no stopping rules for this trial. SAS 9.3 (SAS Institute, Cary, NC, USA) will be used for all analyses.

The primary outcome of the study is t-MoCA trajectories (values of t-MoCA) at postoperative day 2 between the two groups. An unadjusted *t* test (or non-parametric equivalent) will be used to assess superiority. Linear regression will be performed to identify independent predictors of t-MoCA as well as changes in t-MoCA over the 6-month study period. To account for the multiple measurements per subject, we will employ repeated measures regression techniques. Due to flexibility of timing of patient interviews, possibility of censored data and repeated observations, secondary analysis would require the use of a piecewise mixed-effects linear regression model measurement. Interaction will be assessed in the mixed-effects model to test if the t-MoCA slopes are different between groups.

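### The primary day-2 t-MoCA comparison is unadjusted although baseline t-MoCA is collected, so it is valid but gives up precision available at no cost

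*Protocol article*

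**What the plan says.** The Data analysis section takes the t-MoCA value at postoperative day 2 as the primary outcome and names the confirmatory test: "An unadjusted *t* test (or non-parametric equivalent) will be used to assess superiority". The same section plans linear regression to look for predictors of t-MoCA and of its change, and a piecewise mixed model as a secondary analysis. Neither is the superiority test.

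The Sample size calculation section rests on the same unadjusted comparison. Its target is a 2-point difference at day 2 with an SD of 3, tested two-sided at the 5% level with power of 80%, and its result is "we will need 74 subjects in total". Enrolment is set at 100 to cover attrition.

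On the baseline score, the Primary endpoint section says: "Scores on the t-MoCA will be measured preoperatively and postoperatively". The Inclusion and exclusion criteria section excludes patients whose baseline t-MoCA is below 10. A correctly enrolled patient should therefore have a baseline value on the same 22-point scale as the outcome.

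**The concern.** A patient's cognitive score before surgery would be expected to predict the score two days after it. A comparison of raw day-2 values leaves that predictable part of the between-patient variation in the error term. A linear model with baseline as a covariate (ANCOVA) removes it and estimates the same mean difference with a smaller standard error.

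This is a stated choice and not a detail left to an unseen analysis plan. The article itself calls the superiority test unadjusted, so an analysis plan that made the adjusted model primary would depart from it.

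At stake is power in a small trial. The Limitations text describes the assumed effect as relatively large and is concerned about power lost to dropout. The Secondary endpoints section adds that t-MoCA is not assessed while patients are non-verbal in the ICU, so some day-2 scores may be missing. Better precision would give a buffer against fewer evaluable patients, though it would not cure bias from missing scores.

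**Working it through.** **Inputs from the article.** Two-sided α 0.05; power 80%; mean difference 2; SD 3; 74 evaluable (37 per arm); 100 enrolled; 1:1 allocation ("superiority trial of 100 participants with an allocation of 1:1").

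**Assumptions.** SD 3 is the raw SD of the day-2 score. The correlation r between baseline and day-2 scores is not given, so it is shown at 0.3, 0.5 and 0.7.

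**Step 1: reproduce the plan's figure.** For the unadjusted t test with n per arm, SE = 3 × √(2/n), the noncentrality is 2/SE, and df = 2n − 2.
- n = 37: SE = 3 × √(2/37) = 0.70, noncentrality 2.87, df 72, power 80.8%.
- n = 36: power 79.7%.

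The smallest n per arm that reaches 80% is 37, so the total is 74, as stated. The normal approximation gives 72. With all 100 evaluable (50 per arm), SE = 3 × √(2/50) = 0.60 and power is 91.0%.

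**Step 2: adjust for baseline.** The residual SD is 3 × √(1 − r²), and one more degree of freedom is spent (df = 2n − 3). The small extra variance from estimating the slope is ignored.

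| r | Residual SD | Variance removed (r²) | Power, 74 evaluable | Power, 100 evaluable | Total N for 80% power | Detectable difference at 74, 80% power |
|---|---|---|---|---|---|---|
| Unadjusted | 3.00 | – | 80.8% | 91.0% | 74 | 1.98 |
| 0.3 | 2.86 | 9% | 84.3% | 93.3% | 68 | 1.89 |
| 0.5 | 2.60 | 25% | 90.4% | 96.8% | 56 | 1.72 |
| 0.7 | 2.14 | 49% | 97.7% | 99.6% | 40 | 1.41 |

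Example at r = 0.5 and 37 per arm: residual SD = 3 × √0.75 = 2.60; SE = 2.60 × √(2/37) = 0.60; noncentrality = 2/0.604 = 3.31; power 90.4%. If r were 0, the adjusted test would have 80.7% power, so the cost of an uninformative covariate is negligible.

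**Step 3: would a t test on change scores do the same job?** With equal SDs at both times, the SD of the change is 3 × √(2(1 − r)), which is 3.55, 3.00 and 2.32. Normal-approximation power at 37 per arm is then 68%, 82% and 96%. On the same approximation the unadjusted test has 82%, and ANCOVA has 85%, 91% and 98%. The change score loses power at r = 0.3, breaks even at 0.5 and never beats ANCOVA.

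**The case against.** The strongest reply is that nothing here is wrong. The unadjusted test is unbiased under randomization, its type I error is controlled, and the sample size matches it. Power is lost only relative to another method. The gain also depends on a correlation that the article does not report: at r = 0.3 it is about 3 points at 74 evaluable and 2 points if all 100 are evaluable. All of that stands, and it limits the point to efficiency. It is not a reason to keep the unadjusted test as primary, because adjustment costs almost nothing even if r is low.

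A reader might infer more than the article supports in four ways.

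- *That the raw-value test misses the registered outcome.* Table 1 gives the primary outcome as "Change in Telephonic Montreal Cognitive Assessment from baseline up to 6 months". Under randomization the expected baseline means are equal, so the expected arm difference in day-2 values equals the expected arm difference in change to day 2. Raw value, change score and ANCOVA target the same quantity at that time. What differs is the time frame, 6 months against day 2. That is a separate endpoint question, which baseline adjustment does not settle.
- *That chance baseline imbalance is a further harm.* If the baseline SD is also 3 (an assumption), the baseline difference at 37 per arm has an SE of 0.70. At r = 0.5, a one-SE imbalance shifts the unadjusted estimate by 0.5 × 0.70 = 0.35 points. That is half of the estimate's own SE of 0.70 and is already part of it. It restates the precision argument.
- *That the non-parametric alternative makes the p-value data-driven.* The Data analysis section ties non-parametric methods to variables that are not normally distributed, and a condensed article may leave the operating rule to the analysis plan.
- *That the planned regression models already supply the adjustment.* They are not the superiority test.

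**Conclusion.** The point holds as one of efficiency. The primary test is valid and correctly sized, but it sets aside a baseline score that the trial already collects. At 74 evaluable patients, power would be 84%, 90% or 98% instead of 81% for r of 0.3, 0.5 or 0.7. At 100 evaluable it would be 93%, 97% or 99.6% instead of 91%. Equivalently, 80% power would need 68, 56 or 40 patients instead of 74.

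The size rests on two assumptions: the value of r, and SD 3 being the raw day-2 SD. The Sample size calculation section takes its inputs from previous data and a cross walk with the MMSE, and gives no sign that the SD is already a residual or change-score SD. If it were, these gains would not apply as computed. The direction of the gain is not in doubt for any appreciable correlation. The documents do not support a claim that the trial is underpowered on its own assumptions or that its result would be biased for this reason.

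**What to change.** In the Data analysis section, make the primary analysis a linear model of day-2 t-MoCA on randomized arm and baseline t-MoCA, with the adjusted mean difference and its 95% confidence interval as the reported result. Keep the unadjusted t test and a rank-based analysis as sensitivity analyses, both fixed in advance. A t test on change scores should not be the substitute, for the reason in step 3 of the working.

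Leave the sample size unchanged and use the gain as added power or as a buffer against missing day-2 scores. The cost is a sentence or two of analysis wording, settled before any unblinded analysis, with no new data. The time frame in Table 1 should be reconciled with the day-2 outcome as a separate item.

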Secondary analysis of adverse events including incidence of delirium, stroke, myocardial infarction, acute kidney injury (AKI), and hypoxia will also be assessed by employing logistic regression or log-binomial regression for outcomes with an incidence of 10% or greater. Odds ratios or measures of relative risk will include 95% confidence intervals. Secondary outcomes including ADL and GDS values will also be assessed using a trajectory analysis, similar to that employed for t-MoCA scores over time. The harvested biological specimens will provide mechanistic data regarding impact of administered oxygen levels on plasma, urine, and tissue biomarkers. To test this, a linear mixed model will be used to estimate the trajectories of values over the study period. The treatment-by-time interaction will quantify differences in trajectories between the groups. Initial modeling will include participant-specific slope and intercepts with likelihood ratio tests of these variance components considered for model parsimony.

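### The longitudinal t-MoCA model names only a slope-difference test, tied to no segment, and no between-arm contrast at 6 months

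*Protocol article*

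**What the plan says.** The Data analysis section gives the superiority test to an unadjusted comparison of t-MoCA at postoperative day 2. The longer course is left to a secondary piecewise mixed-effects model, chosen because interview timing is flexible and measurements repeat. The between-group test named for that model is: "Interaction will be assessed in the mixed-effects model to test if the t-MoCA slopes are different between groups". No knots are given, and the article does not say whether the preoperative score is a model time point. Linear regression of t-MoCA and of its changes over 6 months is also planned, but its stated purpose is to find predictors, and no treatment contrast or time point is attached to it.

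Testing covers "cognitive testing at baseline, daily from postoperative day 1 until hospital discharge, and then by phone at 1, 3, and 6 months postoperatively". On the expected shape of the curve, the Sample size calculation section says that "postoperative day 2 was reported as the in-hospital postoperative nadir time point". The Abstract extends the primary outcome to 6 months, Table 1 lists it as change from baseline up to 6 months, and the Primary endpoint section justifies 6 months as the end of follow-up.

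The approach is carried over to other scales: "Secondary outcomes including ADL and GDS values will also be assessed using a trajectory analysis, similar to that employed for t-MoCA scores over time".

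**The concern.** If scores fall to a nadir on day 2 and then recover, the slope after day 2 measures how fast patients regain points, not how well they function. Two arms that stay a fixed distance apart have equal slopes. An arm that fell further and then caught up has the steeper slope. Whether patients are cognitively better at 1, 3 or 6 months is a question about levels, or changes from baseline, at those times, and the article names no such comparison for the model.

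Persistence to 6 months is a declared aim, and this model is the natural source for any claim about it. A report that followed the text literally could give a null interaction while the arms still differed at every postoperative visit from day 2. It could also give a significant interaction that a reader would misread as favouring the hyperoxic arm.

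**Working it through.** **The plan's own figure.** Inputs from Sample size calculation: "a two-sided α = 0.05 and 80% power, we will need 74 subjects in total", for a "mean difference in t-MoCA scores of 2 (standard deviation of 3) between the hyperoxia and normoxia group at postoperative day 2". With 37 per arm the noncentrality is 2 / (3 × √(2/37)) = 2.87, and the t-test power is 80.8%. With 36 per arm it is 79.7%. So 37 per arm, 74 in total, is reproduced. With all 100 enrolled at 1:1 (50 per arm), the day-2 test has about 91% power.

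**Scenarios.** Differences are hyperoxic minus normoxic.
- Lasting: a 2-point deficit reached at day 2 and kept to 6 months.
- Recovering: a 2-point deficit at day 2 that shrinks linearly to zero at 6 months.

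**Assumptions not in the document.** Within-patient correlation 0.5, so with SD 3 the between- and within-patient variances are 4.5 each; random intercept only; no missing data.

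**1. Slope after the nadir, 37 per arm.**
- Visits at day 2 and 1, 3 and 6 months: t = 0.07, 1, 3, 6 months; mean 2.52; sum of squared deviations 20.67.
- SE of the slope difference = √(2 × 4.5 / (37 × 20.67)) = 0.108 per month.
- Lasting: true slope difference 0, so rejection is 5%, or 2.5% on each side.
- Recovering: true difference 2 / 5.93 = +0.337 per month; z = 0.337 / 0.108 = 3.1; power = Φ(3.1 − 1.96), about 87%. The steeper slope is in the hyperoxic arm.
- A simulation of 4,000 trials per scenario agrees: 5.1% and 86.5%.

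**2. Baseline-adjusted difference at 6 months, same patients.**
- SE = 3 × √((1 − 0.5²) × 2/37) = 0.604.
- Lasting: z = 2 / 0.604 = 3.3, power about 91% (simulated 90.6%).
- Recovering: true difference 0, rejection about 5% (simulated 5.6%).

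**3. Other readings of the slope test, 50 per arm.** Generalised least squares with visits assumed at days 0, 1 to 5, 30, 90 and 180; correlation 0.6, with the range for 0.4 to 0.8 in brackets.

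| Slope tested | Lasting deficit | Recovering dip |
|---|---|---|
| After day 2 | 0; 5% rejection | +0.34 per 30 days; steeper in hyperoxic arm, over 99% (98-100%) |
| One line over all visits | −0.10 per 30 days; 35% power (25-60%) | +0.23 per 30 days; steeper in hyperoxic arm, 95% (83-100%) |
| Baseline to day 2 | −1 point per day; over 98% in favour of normoxia | −1 point per day; over 98% in favour of normoxia |
| Joint test of both segments (2 df) | about 98% or more | over 99% |

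The zero and the reversed sign after day 2 follow from the shapes of the curves. The assumed correlation changes only the rejection rates where the true slope difference is not zero.

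The last two rows are the informative ones. The fall segment has the right sign in both scenarios, but its value is the same in both, and it largely repeats the day-2 comparison. The joint test also rejects in both, without saying which arm is better at 6 months.

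**The case against.** The strongest reply is that the model is piecewise, so each arm has more than one slope. With randomised arms starting level, a deficit present from day 2 must show up as a slope difference somewhere. If the preoperative score is a model time point and a knot lies near day 2, the fall segment shows it with over 98% power and in the right direction. Read together, the segments separate the cases: a steeper fall with parallel recovery is a lasting deficit, and a steeper fall with steeper recovery is a transient one. This stands. A reader might infer that the planned interaction as a whole misses a lasting deficit. The document does not support that; it is true of the recovery slope and largely true of a single overall slope.

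A reader might also infer that the plan would credit the hyperoxic arm with a benefit. The article asks only whether slopes differ and nowhere counts faster recovery as benefit. Superiority rests on the day-2 test.

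Nor is the interaction the only long-term analysis mentioned: the regression of 6-month changes might capture a lasting deficit, although no group contrast is stated for it.

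For ADL and GDS, no day-2 nadir is stated, and the Follow-up section lists them at the 1-, 3- and 6-month calls. The dip-and-recover argument is not shown to apply to them.

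Knots and similar detail may fairly be left to a fuller document. That does not dispose of the point, because the article does name a test, and no segment slope by itself, nor the joint test, answers the 6-month question.

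**Conclusion.** The point holds in a limited form. The one between-group test named for the longitudinal t-MoCA model concerns slopes, is tied to no segment, and comes with no 6-month contrast of level or change, while the article makes 6 months a declared endpoint. On the recovery segment, the test rejects in 5% of trials for a lasting 2-point deficit, where a baseline-adjusted 6-month contrast has about 91% power. For a dip that recovers, it rejects in about 87% with the steeper slope in the hyperoxic arm, while the 6-month contrast stays at its nominal level. Both comparisons are at 37 per arm. A single overall slope has about 35% power (25-60%) for the lasting deficit at 50 per arm.

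These rates rest on the assumed correlation, visit times, linear recovery, complete data and random intercepts only. Patient-specific slopes or missing visits would change them, but not the zero or the sign on the recovery segment. The weight is moderate, since the analysis is labelled secondary. It would be greater if the 6-month primary outcome in the Abstract and Table 1 is the one that stands.

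**What to change.** Keep the piecewise mixed model, which suits the flexible interview windows. State that its between-group results are the baseline-adjusted mean differences in t-MoCA at day 2 and at 1, 3 and 6 months, each with a 95% CI, taken as fixed-time contrasts from the model. Name 6 months as the key secondary contrast. Report slope differences by segment descriptively, and say that they are not evidence of benefit for either arm. For ADL and GDS, likewise report between-arm differences at 1, 3 and 6 months.

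The cost is analysis wording: the data and the model family stay the same. The output is slightly longer, and there is no longer a single interaction p value to quote.
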